Our primary objective is to test the efficacy of a pharmacological intervention in reducing delirium severity and duration among adults cared for in the ICU. Our primary hypothesis is that, in comparison to usual care, intervention patients will have (1) reduced delirium severity at one week following randomization or hospital discharge, and (2) fewer hospital days with delirium or coma. The secondary hypothesis theorizes that the study intervention will result in (1) shorter hospital lengths of stay, (2) lower ICU, hospital, and 30-day mortality, and (3) lower hospital-acquired complications related to delirium.

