### Planned Analysis

#### Data Analysis

We will conduct intention-to-treat analyses to test the intervention effects on the primary outcomes. No interim analysis is planned for early termination due to efficacy. To formally test for potential harm due to the intervention, 3 interim analyses will be performed using the proposed primary analysis methods after the completion of 0.25, 0.5 and 0.75 of the projected 428 evaluable subjects, using the O'Brien-Fleming boundary, for an overall significance level of 0.05 at study completion.

To test the intervention effect on severity of delirium, we will use the primary outcome of DRS-R-98 severity score on day 8 post-randomization. The primary analysis to test the intervention effect on day-8 DRS-R-98 severity score will be analysis-of-covariance (ANCOVA) with the baseline score as a covariate, after testing and removing any intervention-by-baseline score interaction. If there is a significant interaction, we will test the intervention effect at the mean of the baseline DRS-R-98 severity score. We will use the last observed DRS-R-98 forward to Day 8 as the primary outcome in one analysis. For sensitivity analyses, we will use different methods to impute the missing data. For example, we will impute the missing Day 8 DRS-R-98 severity scores with their worst score on record for patients who have been discharged with delirium or died before day 8. For patients who were hospitalized but could not be evaluated for whatever reason on day 8, we could also interpolate their previous and subsequent DRS-R-98 severity scores to estimate the missing Day 8 score.

We will also test the intervention effect on the repeated measures of DRS-R-98 severity scores using a mixed-effects model. An appropriate contrast for the day 8 effect will be used to corroborate the results of the ANCOVA in the primary analyses. This analysis will provide additional information on the time course of the severity of delirium from its onset in the ICU, with or without intervention.

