To test the intervention effect on duration of delirium, we will compare between groups the number of coma-free and delirium-free days in the first 8 days post-randomization using a two-sample t-test corroborated with the Wilcoxon rank sum test. The intervention effect will be further tested while controlling for patient characteristics using multiple regression. Patients who die before day 8 will have all subsequent days counted as not coma-free or delirium-free. We will impute all days post-discharge as coma-free and delirium-free.

For secondary outcomes, binary measures, e.g. mortality and complications, logistic regression will be used to test the intervention effect, controlling for covariates when appropriate. Highly skewed outcomes such as hospital and ICU length of stay will be compared between groups using nonparametric tests, such as Wilcoxon's rank sum test, and semiparametric survival analyses which can control for covariates.

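### The length-of-stay comparison does not say how in-hospital deaths enter; on raw stay, the named rank-sum test scores an early death as a short, favourable stay

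*Protocol article*

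**What the plan says.** The Background section sets out the secondary hypotheses, among them "shorter hospital lengths of stay, (2) lower ICU, hospital, and 30-day mortality". A shorter stay and fewer deaths are therefore both claimed as benefits.

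The Data Analysis section plans two approaches for stay. The first reads: "Highly skewed outcomes such as hospital and ICU length of stay will be compared between groups using nonparametric tests". Wilcoxon's test is the example that it gives. The second approach, which allows adjustment, is described as "semiparametric survival analyses which can control for covariates". The section does not say what the event is in the survival analysis, whether deaths are censored, or where a death falls in the ranking.

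The same section does set rules for death on other outcomes. For the primary duration outcome: "Patients who die before day 8 will have all subsequent days counted as not coma-free or delirium-free". For the severity score, one sensitivity analysis imputes the "worst score on record for patients who have been discharged with delirium or died before day 8". Mortality has its own test: for "binary measures, e.g. mortality and complications, logistic regression will be used to test the intervention effect".

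**The concern.** Death ends a hospital stay. If stay is simply the number of days until the patient leaves, dead or alive, a patient who dies on day 3 has one of the shortest stays in the trial and the rank-sum test treats that as a good result. The same death counts against the intervention on mortality and for it on stay.

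The error runs both ways. If the intervention raised mortality, stay would move in its favour. If it lowered mortality, as hoped, the added survivors would contribute longer stays and mask a real shortening among patients discharged alive. The Discussion section suggests that the intervention might reduce health care utilization and cost, so the stay result may be read on its own.

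**Working it through.** The article gives no figure for length of stay, so there is nothing to reproduce. The check asks how far deaths alone can move the named test.

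**Inputs from the article.** 428 patients randomised 1:1, so 214 per arm. Table 1 gives ICU mortality of 11% (SICU), 12% (MICU + CCU) and 1.3% (PICU), with 40, 67 and 228 monthly admissions. The admission-weighted rate is (40 × 0.11 + 67 × 0.12 + 228 × 0.013) / 335 = 4.6%; without PICU it is (4.40 + 8.04) / 107 = 11.6%. These are rates for all admissions. Mortality among delirious patients is not given.

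**Assumptions.** Survivors' stay is lognormal with median 12 days in both arms, so there is no true effect on survivors' stay. Patients who die have a lognormal stay with median 6 days. The log-SD is 0.7 for both. One arm has 12% deaths; the other has 12%, 16%, 20% or 24%. The test is two-sided at 0.05.

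**Closed form for the rank-sum on raw stay.**

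1. Chance that a patient who dies has a shorter stay than a survivor: q = Φ[(ln 12 − ln 6) / (0.7 × √2)] = Φ(0.700) = 0.758.
2. Let g be the difference in death proportions. The chance that a random patient from the higher-mortality arm has the shorter stay is 0.5 + (q − 0.5) × g = 0.5 + 0.258g.
3. Standard error of that quantity near the null: √[(2 × 214 + 1) / (12 × 214²)] = 0.0279.
4. Chance of a significant result favouring the higher-mortality arm: 1 − Φ(1.96 − 0.258g / 0.0279).

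| Deaths | g | Shift 0.258g | Shift / SE | Closed form | Simulation |
|---|---|---|---|---|---|
| 12% vs 12% | 0 | 0 | 0 | 2.5% | about 2% |
| 12% vs 16% | 0.04 | 0.0103 | 0.37 | 5.6% | about 5% |
| 12% vs 20% | 0.08 | 0.0206 | 0.74 | 11.1% | about 11% |
| 12% vs 24% | 0.12 | 0.0310 | 1.11 | 19.7% | about 20% |

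**Second set of assumptions.** Time to live discharge has mean 6.0 days (close to Table 1's 5.96 and 6.10 for SICU and MICU + CCU) and log-SD 0.8; mean time to death is 2 or 4 days. The raw rank-sum falsely favoured the higher-mortality arm in about 2% of trials with equal deaths, 8–9% at 5% vs 10%, 6–9% at 11.4% vs 16.4%, and 14–24% at 11.4% vs 21.4%.

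**Survival analysis, same second set, 11.4% vs 21.4%.** A log-rank test stood in for the semiparametric model. With death counted as end of stay, it favoured the higher-mortality arm in 10–15% of trials. With death censored, it favoured that arm in about 1% and the other arm in 3–6%. The direction depends on a coding that the article does not state.

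**Deaths ranked as the longest stay, first set.** Every death now ranks after every survivor, so the chance in step 2 becomes 0.5 − 0.5g. At g = 0.08 the shift is 0.04 / 0.0279 = 1.43 standard errors towards the lower-mortality arm, giving 1 − Φ(1.96 − 1.43) ≈ 30%. At g = 0.12 it is 0.06 / 0.0279 = 2.15, giving about 57%. Simulation gave 28–30% and 56–60%. The higher-mortality arm was favoured in essentially 0%. The false advantage goes, but the test now responds to mortality as well as stay.

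**The case against.** The strongest objection is that this is a condensed article. Its secondary analyses take two sentences, the wording leaves the choice of test open, and event definitions and censoring rules usually sit in an analysis plan, which is not shown. That stands in part: a reader might infer that the trial has no rule for death at all, and the article cannot support that. What remains is that the article names a test which, applied to stay as recorded, misleads in a known direction, while the same section does state how death is handled for delirium-free days. That contrast is softened because delirium-free days are a primary outcome, where more detail is expected.

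A reader might also infer that both planned methods favour the arm with more deaths. The documents do not support that. The survival analysis does so only if death counts as end of stay.

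The size depends on the mortality gap. At 4 points the false-favour rate is about 5%, and the larger figures need gaps of 8 to 12 points. Mortality is tested separately and a safety board reviews data at 25%, 50% and 75% of the sample, so a large excess of deaths would usually be seen. By normal approximation, a mortality comparison with 214 per arm has about 62% power at 12% vs 20% and 91% at 12% vs 24%. This limits the harm but does not remove it: at 12% vs 20%, more than a third of trials would show no significant mortality difference.

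Finally, if the target is resource use, days occupied regardless of vital status is a legitimate quantity. The article does not say that this is the target, and it presents shorter stay as a benefit of treating delirium.

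**Conclusion.** The point holds, with limits. The article names a rank-sum test for hospital and ICU stay without saying how in-hospital deaths enter, and on raw stay that test is distorted towards the arm with more deaths whenever mortality differs. Across 12% vs 16% to 12% vs 24% deaths, false favour to the higher-mortality arm rises from about 5% to about 20% of trials, against a nominal 2.5%. With equal and similarly timed deaths there is no bias. The percentages are illustrative, since they rest on assumed stay distributions, death times and mortality gaps; the direction was the same in every unequal-mortality scenario run. For the survival analysis the conclusion is only that the coding must be stated. Stay is a secondary outcome, and the primary analyses are not touched. This should be put right before analysis but does not threaten the trial's main conclusions.

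**What to change.** State the rule for death before unblinded data are analysed:

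- Define the event as discharge alive and treat death as a competing event. Report the cumulative incidence of live discharge by arm, with patients who die kept as never discharged.
- If a rank test is kept, rank deaths as the longest stay, say that the result is then a composite of stay and mortality, and report it beside the mortality result.
- Show stay among survivors as description only, because it compares groups selected after randomisation.

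The cost is a few sentences of analysis wording. The article says that the medical record system already supplies length of stay and mortality, so no new data are needed. There is a real downside: the target becomes live discharge and no longer bed-days used, and it partly overlaps the mortality outcome. If bed use is also of interest, report total days occupied separately and label it as resource use, not as patient benefit.

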#### Data Safety Monitoring Board

A data safety monitoring board (DSMB) consisting of five members having no participation in the planning or execution of the study will be assembled. The DSMB will be responsible for the oversight of the safety of study patients and to ensure an appropriate sample is collected throughout the study period. The board will review relevant safety data after the completion of data collection of 25%, 50%, and 75% of the planned study sample. During these safety analyses, the DSMB will make recommendations to continue or terminate the progress of the study based on the observed effects of the study intervention.

## Discussion

There are limitations within our study that are worth addressing. First, the potential for contamination exists by randomizing study subjects at the patient level. Physicians may care for patients in both groups and therefore may change behavior based on exposure to the study recommendations. Second, we did not design the study to determine which of the three pharmacologic interventions contributed most significantly to the outcome. Based on our previous experience with e-CHAMP and that of other delirium trials that revealed a small effect size, we chose to evaluate only the impact of the combined pharmacologic intervention. Finally, the impact of the study intervention may be limited by the use of a low dose of haloperidol and the absence of an absolute restriction on anticholinergic and benzodiazepine use. The use of a low dose of haloperidol is a result of our interpretation of the available literature on delirium treatment [16].

Despite these limitations, our study will add valuable information to the scant literature about the hospital care for adults with delirium. First, it provides a focused intervention aimed at the current theory of neurotransmitter imbalances thought to occur during delirium. Second, it provides an opportunity to study the impact of a multi-component intervention not only on delirium duration, but also delirium severity, which few studies have reported until recently. Third, the intervention uses a novel delivery method that provides recommendations at the time of order entry, which is most practical in the ICU environment when the pace of care is at its fastest.

The proposed intervention may result in several benefits considering the impact of delirium on acute and long-term outcomes. It might lead to the development of a universal computerized order entry program that might improve the safety of the current health care system in caring for hospitalized adults with delirium. Our intervention might also decrease health care utilization and cost of the current health care system by reducing days with delirium. Additionally, a successful delirium intervention may also help physicians deliver better care for their patients and increase their trust in the use of information technology as a tool to help their patients.

## List of Abreviations

ICU: intensive care unit; GABA: gamma-aminobutyric acid; IRB: institutional review board; WMH: Wishard Memorial Hospital; MICU: medical intensive care unit; SICU: surgical intensive care unit; CCU: coronary intensive care unit; PICU: progressive intensive care unit; RASS: Richmond Agitation-Sedation Scale; CAM-ICU: confusion assessment method for the intensive care unit; CDSS: computerized decision support system; eCHAMP: enhancing care of hospitalized older adults with memory problems; PMD: Pharmacologic Management of Delirium; RMRS: Regenstrief Medical Record System; SAA: serum anticholinergic activity; ACB: anticholinergic cognitive burden; SCCM: Society of Critical Care Medicine; DRS-R-98: Delirium Rating Scale revised 1998; IQCODE: Informant questionnaire on cognitive decline in the elderly; APACHE: acute physiology and chronic health evaluation; SAE: serious adverse event; EPS: extrapyramidal symptom; ANCOVA: analysis of covariance; DSMB: data safety monitoring board; ER: emergency room
